# Behavioural Activation Therapy for Depression after Stroke (BEADS): a study protocol for a feasibility randomised controlled pilot trial of a psychological intervention for post-stroke depression

**DOI:** 10.1186/s40814-016-0072-0

**Published:** 2016-08-10

**Keywords:** Stroke, Depression, Post-stroke depression, Psychological intervention, Behavioural activation, Feasibility, Randomised controlled trial, Complex intervention

## Abstract

**Background:**

There is currently insufficient evidence for the clinical and cost-effectiveness of psychological therapies for treating post-stroke depression.

**Methods/Design:**

BEADS is a parallel group feasibility multicentre randomised controlled trial with nested qualitative research and economic evaluation. The aim is to evaluate the feasibility of undertaking a full trial comparing behavioural activation (BA) to usual stroke care for 4 months for patients with post-stroke depression. We aim to recruit 72 patients with post-stroke depression over 12 months at three centres, with patients identified from the National Health Service (NHS) community and acute services and from the voluntary sector. They will be randomly allocated to receive behavioural activation in addition to usual care or usual care alone. Outcomes will be measured at 6 months after randomisation for both participants and their carers, to determine their effectiveness. The primary clinical outcome measure for the full trial will be the Patient Health Questionnaire-9 (PHQ-9). Rates of consent, recruitment and follow-up by centre and randomised group will be reported. The acceptability of the intervention to patients, their carers and therapists will also be assessed using qualitative interviews. The economic evaluation will be undertaken from the National Health Service and personal social service perspective, with a supplementary analysis from the societal perspective. A value of information analysis will be completed to identify the areas in which future research will be most valuable.

**Discussion:**

The feasibility outcomes from this trial will provide the data needed to inform the design of a definitive multicentre randomised controlled trial evaluating the clinical and cost-effectiveness of behavioural activation for treating post-stroke depression.

**Trial registration:**

Current controlled trials ISRCTN12715175

## Background

Depression is the most commonly investigated emotional consequence of stroke [1] with an average prevalence of 29 %, which remains consistent up to 10 years post-stroke [2]. Effective treatment of depression is important because depression is associated with increased healthcare utilisation [3], worse rehabilitation outcomes [4–7], increased carer strain [8] and increased mortality [2, 9]. Co-morbid long-term physical health conditions and mental health problems have been found to increase health care costs [10]. Stroke patients who are depressed may engage less in rehabilitation, which in turn can lead to decreased functional recovery [7]. Post-stroke depression is also associated with lower quality of life [2, 11]. Thus, in addition to improving mood, effective treatment of post-stroke depression is important because it has the potential to improve patients’ functional outcomes and quality of life and also reduce strain on their carers. About one third of stroke patients have aphasia [12, 13] and approximately 70 % will have cognitive impairment [14, 15]. Aphasia can affect all communication modalities including speaking, understanding, reading and writing. Stroke survivors with aphasia may be particularly susceptible to post-stroke depression [16, 17].

There is currently insufficient evidence for the clinical and cost-effectiveness of psychological therapies for treating post-stroke depression [18]. Trials of brief psychosocial behavioural intervention plus antidepressant [19] and motivational interviewing [20, 21] reduced post-stroke depression but these studies recruited patients early after stroke and excluded those with severe communication or cognitive problems, so these findings may not be applicable to all patients with post-stroke depression. There is evidence from single-case design studies that some patients with post-stroke depression improve following cognitive behavioural therapy (CBT) [22, 23]. However, the only randomised controlled trial of CBT for post-stroke depression found no significant difference between those patients who received CBT, an attention placebo or usual care [24].

A psychological intervention which may be suitable for stroke patients is behavioural activation (BA) therapy. BA is based on the behavioural model of depression, where depression is believed to result from a lack of response-contingent positive reinforcement [25]. Positive reinforcement is dependent on the person’s actions [26] and reduction in activity can lead to loss of reinforcement. Stroke can result in a loss or restriction of rewarding activities and interactions (such as everyday activities, hobbies and social interactions) and this loss may lead to depression. BA aims to increase activity level, particularly the frequency of pleasant events, to improve mood. BA is effective at treating depression in adults in primary care settings, older adults and patient/carer dyads with dementia, and has comparable effectiveness to CBT [27–32].

A multicentre randomised controlled trial, the Communication and Low Mood: CALM trial [33] (*n* = 105) evaluated BA, delivered by an assistant psychologist, for treating low mood in stroke patients with aphasia. This found that mood was significantly better at 6-month follow-up in those who received BA compared to usual clinical care. The transferability of BA to hard-to-reach populations, such as those with aphasia and severe cognitive problems [34, 35], adds to its potential as a psychological intervention after stroke. Given that the CALM trial demonstrated that it was possible to deliver BA to a group of patients usually excluded from psychological interventions, there is significant potential for using BA for treating all stroke patients with depression.

However, as the CALM trial was not conducted with the wider stroke population, a more robust pilot study is now required to inform any future proposal for a definitive multicentre randomised controlled trial (RCT) evaluating the clinical and cost-effectiveness of BA for treating post-stroke depression [36–38]. Therefore, the BEADS trial is looking at the feasibility of delivering BA to all patients with post-stroke depression and the feasibility of proceeding to a definitive trial. This study will provide information on feasibility and clinical outcomes of BA for treating post-stroke depression and its acceptability to patients, carers and therapists. The results of this study will also provide data on the feasibility of delivering the BA intervention in the National Health Service (NHS) as part of routine clinical practice.

### Objectives

The overarching aim of the BEADS trial is to explore the feasibility of a study to investigate the clinical and cost-effectiveness of behavioural activation therapy for people with post-stroke depression. The primary objective is to determine the feasibility of proceeding to a definitive trial, based onFeasibility of recruitment to the main trialAcceptability of the research procedures and measuresAppropriateness of the baseline and outcome measures for assessing impactRetention of participants at outcomePotential value of conducting the definitive trial, based upon value of information analysis

The secondary objective is to determine the feasibility of delivering the behavioural activation therapy intervention with patients with post-stroke depression, based onAcceptability of behavioural activation therapy to participants, carers and therapistsFeasibility of delivering the intervention by assistant psychologists or low-intensity psychological wellbeing practitioners under the supervision of an experienced mental health practitionerDocumentation of ‘usual care’ using a healthcare resource use questionnaireTreatment fidelity of the behavioural activation therapyFeasibility of delivery of behavioural activation therapy within current services and within a definitive trialEstimate the sample size required for the main RCT

## Methods/Design

BEADS is a parallel group feasibility multicentre randomised controlled trial design, with nested qualitative research, comparing behavioural activation therapy to usual stroke care for patients with post-stroke depression.

### Setting and participants

Participants will be recruited from three centres (Sheffield, Derby, and Mansfield). Participants will be identified through NHS hospital stroke databases, community stroke team databases, hospital stroke wards, caseloads of community and acute stroke teams and the voluntary sector (stroke and aphasia groups).

Participants will be included in the study if theyHave a diagnosis of ischaemic or haemorrhagic strokeAre aged 18 years or overAre living in community settings (including nursing homes)Are a minimum of 3 months and a maximum of 5 years post-stroke andAre identified as depressed. Depression is defined in two ways:For participants who are able to complete the Patient Health Questionnaire-9 (PHQ-9 [39]): a score of ≥10 on the PHQ-9, or;For participants with communication difficulties or severe cognitive difficulties who are unable to complete the PHQ-9: a score of at least 50/100 on Visual Analog Mood Scales (VAMS) Sad item [40]

Participants will be excluded from the study if theyHad a diagnosis of dementia prior to the stroke (based on self-report by patient/carer)Were receiving medical or psychological treatment for depression at the time at which they had their stroke (based on self-report by patient/carer)Are currently receiving psychological interventionHave communication difficulties that would impact on their capacity to take part in the intervention (based on assessment with the Consent Support Tool [41] for people with aphasia)Have visual or hearing impairments that would impact on their capacity to take part in the intervention (based on the therapist’s discretion at baseline assessment)Were unable to communicate in English prior to the stroke or do not have mental capacity to consent to take part in the trial.

The criteria are designed to identify those who would be suitable for the intervention were it to be offered within clinical practice. All reasons for patient exclusion will be recorded.

### Recruitment

The specific process for recruitment will vary according to where the participant is recruited from. Clinical teams will send invitation letters to those on the hospital or community stroke databases of discharged patients. Patients will be sent a postal pack containing a covering letter, participant information sheet, reply slip, PHQ-9, VAMS Sad and prepaid envelope. Patients who are interested in taking part will return the completed PHQ-9 and VAMS Sad with the reply slip and this will be taken as implied consent to subsequent contact by the therapist. Those who are identified as not being depressed will be contacted by the therapist to be thanked for their interest and will be informed that they are not eligible. People who score as depressed but decline to participant or are identified as not meeting the remainder of the inclusion criteria then they would be advised to contact their GP. The therapist will contact patients classified as depressed to arrange a visit to check the participant meets the remainder of the inclusion criteria, to explain the study and formally invite those who are eligible to take part. At this point, they will also obtain informed consent and complete baseline assessments.

Alternatively, research nurses will visit hospital stroke wards, and members of the community and acute stroke teams will be asked to identify potential participants and seek their permission to be contacted by the research team. The therapist at each centre will also seek permission to attend stroke and aphasia groups in their locality to explain the study to group members in order to identify potential participants. Willing patients will then be contacted by phone to tell them more about the research and arrange a home visit during which they will complete the screening measures, or they can request a postal recruitment pack. During the home visit (or by post), those patients who are identified as not being depressed will be thanked for their interest and will be informed that they are not eligible. For patients who are classified as depressed, the therapist will either (a) arrange a subsequent home visit or (b) continue with recruitment of the participant. Informed consent will be taken from eligible patients, who can then be entered into the study and randomised accordingly (See Fig. 1).

**Fig. 1 Fig1:**
[figure not shown]
Flow of participants through the trial

Self-referrals will be facilitated by advertising the study in newsletters of relevant charities and societies. Posters will also be displayed in local voluntary sector groups, libraries and local community centres so that potential participants can contact the local research team. The methods of identifying potential participants have been kept broad to allow assessment of the optimum recruitment strategy for the definitive study.

Carers of trial participants will be recruited via the trial participants during the initial home visit. They will be asked to complete the baseline and 6-month outcome assessment questionnaires.

### Randomisation and blinding

Participants will be randomised at baseline (after informed consent and baseline assessments) in equal proportions to BA or usual stroke care. Several clinical assessments will be taken at baseline: socio-demographic and stroke characteristics; Frenchay Aphasia Screening Test [42]—to assess communication difficulties; Montreal Cognitive Assessment [43]—to screen for cognitive impairment; and the Modified Rankin Scale [44]—to assess overall disability. These measures will be used to describe the baseline characteristics of the recruits.

Randomisation will be stratified by centre and will be conducted using a computer-generated pseudo-random list with random permuted blocks of varying sizes, on a remote, secure internet-based randomisation system created and hosted by the Sheffield Clinical Trials Research Unit (CTRU). Once a participant has consented to the study, the therapist will log into the randomisation system and enter basic demographic information. After this information has been entered, the allocation for that participant will then be revealed to the therapist. Access to the allocation sequence will be restricted to those with authorisation. The sequence of treatment allocations will be concealed until interventions have been assigned and recruitment, data collection and analyses are complete.

It is not possible pragmatically for the participant or therapist to be blind to the group allocation, but the researcher completing 6-month outcome assessments will be blinded and will also have had no involvement in any other aspects of the trial. The researcher will be asked to record whether or not they think they were unblinded and will also be asked to guess the group allocation. We will follow guidelines to minimise unblinding during randomised controlled trials of rehabilitation [45, 46].

### Ethical issues

The trial will be conducted in accordance with the ethical principles that have their origin in the Declaration of Helsinki, 1996; the principles of Good Clinical Practice, and the Department of Health Research Governance Framework for Health and Social Care, 2005. Participants will not be paid to participate in the trial. Ethical approval to conduct the study was granted by the National Research Ethics Service Committee for East Midlands—Leicester (ref 15/EM/0014). Local NHS Research and Development approvals have also been given for each participating centre. All trial staff and investigators will endeavour to protect the rights of the trial’s participants to privacy and informed consent and will adhere to the Data Protection Act, 1998.

### Informed consent

Written informed consent will be obtained from all participants who are able to give it. Those who lack the mental capacity to give consent are excluded from the trial. The therapists will explain the details of the trial and provide a participant information sheet, ensuring that the participant has sufficient time to consider participating or not. Informed consent to participate in the trial will be taken before participants undergo any interventions relating to the study. For patients who are physically unable to sign the form (e.g. weakness in dominant hand due to stroke) then consent will be given using a mark or line in the presence of an independent witness (who has no involvement in the trial) who will then corroborate by signing the consent form.

A significant proportion (up to 50–80 %) of the stroke population have some degree of cognitive or language impairment—aphasia. The level of support required to enable a person with aphasia to provide informed consent is dependent upon the severity and profile of the aphasia. In order to provide information in a format consistent with each individual’s language ability, a Consent Support Tool (CST) [41] will be used. The therapist will request verbal consent from the potential participant to carry out part A of the CST to determine how appropriate it is to provide the accessible information sheet. If the CST indicates that the potential participant understands less than two key written or spoken words in a sentence, they are likely to find it difficult to understand all the information required to provide informed consent. These participants will be thanked for their time but are not eligible for the study as, despite the intervention using techniques to support the inclusion of those people with reduced language or cognition, the intervention does rely on achieving understanding with support and actively participating in therapeutic communication.

The accessible information sheet will be provided to those who understand at least two key written and spoken words. This follows standard aphasia-friendly principles with one idea presented per page in short simple sentences in large font. Keywords are emboldened and each idea is represented by a pictorial image to support understanding of what the study is about. The therapists will be trained to support understanding further by reading parts of the information aloud and using supportive gestures/actions.

Once the potential participant has been given the information and had sufficient time to ask questions and discuss with family or friends, the therapist will check the individual has capacity to provide informed consent by checking that they understand the information, that they can remember what the study is about and clearly express their decision in the way in which they usually communicate (speaking, writing, using a communication aid). Participants with capacity to provide informed consent who have used the accessible information provision will be provided with an aphasia-friendly consent form and asked to initial all boxes before signing. Where stroke symptoms prevent initialling of boxes or providing written consent, the patient will use a mark or line and a relative/friend should be asked to witness the fact that the participant is consenting to the study and sign and date the consent form to confirm this on behalf of the participant.

Written informed consent will also be taken from carer and therapist participants for the outcome assessments and qualitative interviews. Should there be any subsequent amendment to the final protocol, which might affect a participant’s participation in the trial, continuing consent will be obtained using an amended consent form that will be signed by the participant.

Participants have the right to withdraw from the study at any time. Individuals removed from active participation in the intervention will not be replaced. Reason for withdrawal from the intervention, if known, will be recorded. Participants may be withdrawn from the trial either at their own request or at the discretion of the investigator. The investigator may withdraw a participant in the interest of the participant or due to a deviation from the protocol. Participants may discontinue their allocated intervention or withdraw from the study for the following reasons: withdrawal of consent; changes to their health status preventing their continued participation or failure to adhere to protocol requirements. The participants will be made aware that this will not affect their current or future care. Participation in the study does not mean that access to other services, which are part of usual care, will be compromised.

More specifically, if during the trial there is a patient allocated to the BEADS intervention who subsequently needs clinical psychology input (as per the protocol of the local service) then the BEADS therapist (AP/PWP) will discuss this with the clinical psychologist or clinical lead and the patient and will agree what is best for the patient. If it is agreed that the patient needs immediate clinical psychology input then they would be withdrawn from the BEADS intervention and they will see the clinical psychologist, or be referred to alternative provision, as appropriate to that patient. The patient will be withdrawn from the intervention but not the overall trial, i.e. we will still be able to collect outcome data from them. We will record the number of patients who we withdraw from the BEADS intervention because of a conflict with clinical services.

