#### Data analysis

All trial analyses will be conducted according to an a priori statistical analysis plan that will be prepared during the early stages of the trial in agreement by the Trial Management Group, Trial Steering Committee and the Data Monitoring and Ethics Committee. Primary analysis will be conducted on the intention-to-treat population; however, exploratory analysis may be conducted excluding patients who do not comply with the protocol.

As the trial is a pragmatic parallel group, the data will be reported and presented according to the CONSORT 2010 statement [61]. As a feasibility study the main analysis will be descriptive and focus on confidence interval estimation and not formal hypothesis testing and will be guided by the Thabane et al. (2010) checklist for reporting of pilot trials [37]. Rates of consent, recruitment and follow-up by centre and by randomised group will be reported. Outcome measures will be summarised overall and by randomised group, to inform sample size estimation for the definitive trial. The data from this feasibility study will be used to estimate the consent rate, attrition rate and the variability of the continuous outcomes in the trial population and use this information to inform the sample size calculation for the definitive RCT. Study site will be treated as a covariate in an adjusted analysis where we estimate the treatment effect adjusted for baseline score and site. Since the intervention is therapist led, the data will be used to estimate the intra-cluster correlation coefficient for patients treated by the same therapist using a marginal or random effects model for the 6-month post-randomisation PHQ-9 outcome.

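### The withdrawal rules let the investigator take participants out of the trial for protocol deviation and do not guarantee their 6-month outcome, in tension with the intention-to-treat analysis and the retention estimate

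*Protocol article*

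**What the plan says.** Three consecutive statements in the protocol article, section Informed consent, set the rule. The first gives the scope: "Participants may be withdrawn from the trial either at their own request or at the discretion of the investigator". The second gives the investigator's grounds: "The investigator may withdraw a participant in the interest of the participant or due to a deviation from the protocol". The third opens "Participants may discontinue their allocated intervention or withdraw from the study for the following reasons", and its list includes "failure to adhere to protocol requirements". That one list covers both stopping the intervention and leaving the study.

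The same section then treats one situation separately. A BA participant who needs immediate clinical psychology input is "withdrawn from the intervention but not the overall trial, i.e. we will still be able to collect outcome data from them".

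Under Data analysis the article says: "Primary analysis will be conducted on the intention-to-treat population". Leaving out people who do not comply is allowed there only as an exploratory analysis. Retention at outcome is one of the bases of the primary objective (Objectives). The attrition rate is to inform the sample size of the definitive trial, and retention is among the evidence on whether that trial is feasible (Data analysis).

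**The concern.** The authors distinguish stopping treatment from leaving the trial, but they apply the distinction to one case. For deviation and non-adherence the two outcomes are left joined, and the investigator may choose the one that ends participation.

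Two things are at stake. First, people whom the analysis section would set aside only in an exploratory analysis can be lost during conduct. They may stay nominally in the intention-to-treat set, but without a 6-month PHQ-9, and no analysis plan can recover an outcome that was never collected. Second, observed attrition may combine participants' own drop-out with discretionary removal. The definitive trial needs to know the former.

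The loss could differ by arm. BA involves up to 15 sessions and between-session tasks (Intervention arm), while usual-care participants have no contact with the trial therapist (Control arm). Therapists also know the allocation (Randomisation and blinding). The article uses the estimated PHQ-9 difference as confirmation that a definitive trial is worthwhile, so a selective loss would matter even though the study is not powered for efficacy.

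**Working it through.** **Reading the text**

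1. Scope: the first sentence says withdrawal from the trial, and the grounds follow at once. Protocol deviation is therefore a ground for trial-level withdrawal, not only for stopping therapy.
2. Consequence: in the clinical psychology case, staying in the overall trial is explained as still being able to collect outcomes. By contrast, leaving the trial would mean that they are not collected. This is an inference; no sentence says it outright.
3. Against Data analysis: non-compliers belong in the primary analysis, yet the consent section permits their removal before outcome.

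**The plan's own figures**

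Inputs from Sample size calculation: 60 evaluable, 15% attrition, 72 recruited, standard deviation (SD) precision about ±19%. Allocation is equal, so 36 per arm.

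- Recruitment: 60 / (1 − 0.15) = 70.6, so 71. The stated 72 agrees closely and divides evenly into 24 per centre and 36 per arm.
- SD precision at n = 60: the chi-square 95% interval for the true SD runs from 0.848 to 1.220 times the observed SD. The half-width is (1.220 − 0.848)/2 = 18.6%. The approximation 1.96/√(2 × 59) gives 18.0%. Both agree with the stated figure.

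Neither figure is in dispute.

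**Illustration of removals**

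Expected follow-up is 72 × 0.85 = 61.2, taken as 61. Let k be the number of investigator removals added to the 15%. The article gives no such rate, so k is an assumption. Retention is (61 − k)/72, and recruitment needed for 60 evaluable is 60 divided by that retention.

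| k | Followed up | Retention | SD half-width | Recruits needed for 60 |
|---|---|---|---|---|
| 0 | 61 | 84.7% | 18.4% | 71 |
| 3 | 58 | 80.6% | 18.9% | 75 |
| 6 | 55 | 76.4% | 19.5% | 79 |
| 8 | 53 | 73.6% | 19.9% | 82 |

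If all removals fell in the BA arm, its expected follow-up of 36 × 0.85 = 30.6 would drop to 27.6/36 = 76.7% (k = 3) or 24.6/36 = 68.3% (k = 6).

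**Effect on the treatment difference**

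Suppose k participants are removed from BA alone and would have scored 0.5 SD differently from those kept (assumed, in either direction). The BA mean then shifts by (k/30.6) × 0.5: 0.05 SD for k = 3 and 0.10 SD for k = 6. For scale, the 95% interval for the difference with 30 per arm has a half-width of about 1.96 × √(2/30) = 0.51 SD.

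**The case against.** The strongest reply is that the stop in outcome collection is inferred. The clinical psychology paragraph is introduced as a more specific case, so it can be read as an example of the general rule rather than its only exception. The clause says may, and the shared list does not say that non-adherence must lead to leaving the study. Data analysis also presupposes that non-compliers are in the dataset, since otherwise there would be no one to exclude in the exploratory analysis. A journal article condenses a fuller protocol, which may settle the matter.

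Most of this stands, and it rules out four stronger readings that a reader might infer:

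- That the rule removes the outcome and so flatly contradicts intention-to-treat. The text permits such a loss; it does not require it.
- That only BA participants can be removed. Neither deviation nor protocol requirements are confined to therapy. No minimum number of sessions is set, so attending few sessions is not clearly a deviation.
- That the result is biased towards BA, in effect or in costs. This needs removed participants to do worse or cost more, and the article says neither.
- That a go/no-go threshold for retention is compromised. No threshold is stated, and retention is weighed with other evidence.

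It is also fair that the removal rates are assumed, that some removals may already be counted in the 15%, and that a shift of 0.05–0.10 SD is small beside an interval half-width of about 0.51 SD.

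The permission itself is not answered. This is a rule that the article states, not a detail left out in condensing, and its wording allows a loss that the analysis section does not intend.

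**Conclusion.** The point holds as a tension between a permissive withdrawal rule and the planned analysis. Trial-level withdrawal for deviation is explicit. That outcome collection then ends is inferred from the contrast within the same section. The main exposure is the retention and attrition estimate: under the assumed 3 to 8 extra removals, overall retention falls by about 4 to 11 percentage points. SD precision barely moves. Loss could be unequal between arms, but the size and direction of any bias in the PHQ-9 difference are unknown. The matter is worth correcting because the correction is cheap and the lost data cannot be recovered later.

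**What to change.** Reconcile Informed consent with Data analysis:

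- State that protocol deviation or non-adherence alone does not end outcome collection.
- State that the 6-month outcome is sought from every randomised participant unless consent to follow-up is withdrawn, the participant dies, or follow-up is judged not to be in the participant's interest. The last exception keeps the investigator's existing discretion in a population with recognised risks of distress and suicide.
- Report intervention discontinuation, investigator withdrawal from the trial and loss to follow-up as three separate rates by arm, so that the attrition carried into the definitive trial's sample size can be interpreted.

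No position is taken on when treatment should stop.

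The cost is a short wording change plus tracing and assessing a few participants whose 6-month visits are already planned. The target of 72 is unchanged. Recruitment was planned to run to the end of April 2016, so the last 6-month assessments would fall around the end of October 2016, after the article's publication in August 2016. The clarification could therefore still have applied to some participants, and the separate reporting to all.
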